***Interviewer:***

→ Now I would like to ask you some questions about your relationships with people at this camp. As you know, your camp provided our research team with a list of the camp members. We used this list to identify camp members, like you, to participate in the study. I would like to ask you to identify the camp members that you know from this list. We will then ask you a few questions about your close friends in this camp. Our team will be asking other camp members to answer similar questions, but we will never reveal anybody’s answers to anybody else. Just as I won’t tell you what any of the other camp members said about you, I will not tell other camp members anything that you say in this interview.

FOR EACH CAMP MEMBER ON THE ROSTER, ASK:

| **No.** | **Questions and Filters** | **Coding Categories** | **Codes** | **Skip to:** | **VARIABLE** |
| --- | --- | --- | --- | --- | --- |
| ***Interviewer:***  → *I would first like you to identify all the people on this list that you know.* | | | | | |
| Q1201 | Do you know this person? | NO  YES | 0  1 | **For person, if participant indicates “NO”, do not ask Q1202 for that person.** | KNOWP |
| ***Interviewer:***  → *Now, for all the camp members you know, I would like you to identify what relationship you have with each person.* | | | | | |
| Q1202 | What relationship do you have with this person? | FRIEND  ACQUAINTANCE  SOMEBODY I DON’T GET ALONG WITH | 1  2  3 |  | RELP |
| ***Interviewer:***  → Now I’d like to ask you some questions about your friends in this camp. You mentioned that these people are your friends: [HAVE COMPUTER LIST THE NAMES OF PEOPLE THEY MENTIONED WERE THEIR FRIENDS] | | | | | |
| Q1203 | Aside from your girlfriend/boyfriend, from the people on this list, who is your closest friend? [PARTICIPANT SELECTS FRIEND 1]  NOTE that the participant should not select his/her boyfriend or girlfriend, as we will ask about that relationship later. | PID |  |  | FRND1 |
| Q1204 | Who is your second closest friend out of the people on this list? [SELECTS FRIEND 2] | PID |  |  | FRND2 |
| Q1205 | Who is your third closest friend out of the people on this list? [SELECTS FRIEND 3] | PID |  |  | FRND3 |
| ***Interviewer:***  → Now you are going to be asked some questions about your two closest friends in your camp. Remember that no information you provide will be shared with anyone outside of our research team. I will start by asking you about FRIEND 1. | | | | | |
| Q1206 | Is FRIEND 1 a man or a woman? | MAN  WOMAN | 1  2 |  | GEND_F1 |
| Q1207 | In addition to friendship, do you have any of the following other relationships with FRIEND 1?  PAST  GIRLFRIEND/BOYFRIEND  HAD SEX, BUT NOT BOYFRIEND/GIRLFRIEND  SISTER/BROTHER  COUSIN  OTHER RELATIVE  CO-WORKER  CO-OWNER OF BUSINESS  OTHER___________________ | NO  YES | 0  1 |  | O_PGBF_F1  O_SEX_F1  O_SIB_F1  O_COS_F1  O_FAM_F1  O_CWK_F1  O_CBUS_F1  O_REL_F1  O_REL_F1_S |
| Q1208 | How long have you known FRIEND 1? | MORE THAN 3 YEARS  1-3 YEARS  6-12 MONTHS  LESS THAN 6 MONTHS, BUT MORE THAN 1 MONTH  1 MONTH OR LESS | 1  2  3  4  5 |  | KNOWF1 |
| Q1209 | How close do you feel towards FRIEND 1? | VERY CLOSE  SOMEWHAT CLOSE  NOT VERY CLOSE | 1  2  3 |  | CLOSEF1 |
| Q1210 | How much do you trust FRIEND 1? | A LOT  SOMEWHAT  NOT VERY MUCH  NOT AT ALL | 1  2  3  4 |  | TRUSTF1 |
| Q1211 | Where do you mostly meet FRIEND 1?  Please select the 1 location where you meet FRIEND 1 the most. | SCHOOL  WORK  CAMP  MOSQUE/CHURCH  STREET  CLUB/BAR  GUEST HOUSE/HOTEL  BEACH/PARTY  HOME  OTHER___________________ | 1  2  3  4  5  6  7  8  9  10 |  | MEETF1  MEETF1_S |
| Q1212 | Do you think FRIEND 1 uses condoms all the time? | NO  YES | 0  1 |  | CNDUSEF1 |
| Q1213 | Do you think FRIEND 1 thinks that he/she should be using condoms all the time? | NO  YES | 0  1 |  | CNDINJF1 |
| Q1214 | Has FRIEND 1 encouraged you to use condoms all the time? | NO  YES | 0  1 |  | CNDADVF1 |
| Q1215 | Do you think FRIEND 1 has more than one sexual partner at the same time? | NO  YES | 0  1 |  | MCPF1 |
| Q1216 | Do you think FRIEND 1 thinks that it’s ok for him/her to have more than one sexual partner at the same time? | NO  YES | 0  1 |  | MCPINJF1 |
| Q1217 | Has FRIEND 1 discouraged you from having more than one sexual partner at the same time? | NO  YES | 0  1 |  | MCPADVF1 |
| Q1218 | Do you think FRIEND 1 hits his sexual partner? | NO  YES | 0  1 | **ASK ONLY IF Q1206 = 1** | IPVF1 |
| Q1219 | Do you think FRIEND 1 thinks there are some situations in which it’s ok to hit his sexual partner? | NO  YES | 0  1 | **ASK ONLY IF Q1206 = 1** | IPVINJF1 |
| Q1220 | Do you think FRIEND 1 gets hit by her sexual partner? | NO  YES | 0  1 | **ASK ONLY IF Q1206 = 2** | VVF1 |
| Q1221 | Do you think FRIEND 1 thinks there are some situations in which it’s ok for her to be hit by her sexual partner? | NO  YES | 0  1 | **ASK ONLY IF Q1206 = 2** | VVINJF1 |
| Q1222 | Has FRIEND 1 discouraged you from hitting your sexual partner? | NO  YES | 0  1 | **ASK ONLY IF Q101 = 1** | IPVADVF1 |
| Q1223 | Has FRIEND 1 encouraged you to request that your sexual partner not hit you? | NO  YES | 0  1 | **ASK ONLY IF Q101 = 2** | VVADVF1 |
| Q1224 | Do you think FRIEND 1 ever had an HIV test? | NO  YES | 0  1 |  | HIVTSTF1 |
| Q1225 | Do you think FRIEND 1 thinks that he/she should have an HIV test? | NO  YES | 0  1 |  | HIVINJF1 |
| Q1226 | Has FRIEND 1 encouraged you to get an HIV test? | NO  YES | 0  1 |  | HIVADVF1 |
| Friend 2  ***Interviewer:***  → I would now like to ask you the same questions, expect now I would like you to think about Friend 2. | | | | | |
| Q1227 | Is FRIEND 2 a man or a woman? | MAN  WOMAN | 1  2 |  | GEND_F2 |
| Q1228 | In addition to friendship, do you have any of the following other relationships with FRIEND 2?  PAST  GIRLFRIEND/BOYFRIEND  HAD SEX, BUT NOT BOYFRIEND/GIRLFRIEND  SISTER/BROTHER  COUSIN  OTHER RELATIVE  CO-WORKER  CO-OWNER OF BUSINESS  OTHER___________________ | NO  YES | 0  1 |  | O_PGBF_F2  O_SEX_F2  O_SIB_F2  O_COS_F2  O_FAM_F1  O_CWK_F2  O_CBUS_F2  O_REL_F2  O_REL_F2_S |
| Q1229 | How long have you known FRIEND 2? | MORE THAN 3 YEARS  1-3 YEARS  6-12 MONTHS  LESS THAN 6 MONTHS, BUT MORE THAN 1 MONTH  1 MONTH OR LESS  DON’T KNOW | 1  2  3  4  5  88 |  | KNOWF2 |
| Q1230 | How close do you feel towards FRIEND 2? | VERY CLOSE  SOMEWHAT CLOSE  NOT VERY CLOSE | 1  2  3 |  | CLOSEF2 |
| Q1231 | How much do you trust FRIEND 2? | A LOT  SOMEWHAT  NOT VERY MUCH  NOT AT ALL | 1  2  3  4 |  | TRUSTF2 |
| Q1232 | Where do you mostly meet FRIEND 2?  Please select the 1 location where you meet FRIEND 2 the most. | SCHOOL  WORK  CAMP  MOSQUE/CHURCH  STREET  CLUB/BAR  GUEST HOUSE/HOTEL  BEACH/PARTY  HOME  OTHER___________________ | 1  2  3  4  5  6  7  8  9  10 |  | MEETF2  MEETF2_S |
| Q1233 | Do you think FRIEND 2 uses condoms all the time? | NO  YES | 0  1 |  | CNDUSEF2 |
| Q1234 | Do you think FRIEND 2 thinks that he/she should be using condoms all the time? | NO  YES | 0  1 |  | CNDINJF2 |
| Q1235 | Has FRIEND 2 encouraged you to use condoms all the time? | NO  YES | 0  1 |  | CNDADVF2 |
| Q1236 | Do you think FRIEND 2 has more than one sexual partner at the same time? | NO  YES | 0  1 |  | MCPF2 |
| Q1237 | Do you think FRIEND 2 thinks that it’s ok for him/her to have more than one sexual partner at the same time? | NO  YES | 0  1 |  | MCPINJF2 |
| Q1238 | Has FRIEND 2 discouraged you from having more than one sexual partner at the same time? | NO  YES | 0  1 |  | MCPADVF2 |
| Q1239 | Do you think FRIEND 2 hits his sexual partner? | NO  YES | 0  1 | **ASK ONLY IF Q1227 = 1** | IPVF2 |
| Q1240 | Do you think FRIEND 2 thinks there are some situations in which it’s ok to hit his sexual partner? | NO  YES | 0  1 | **ASK ONLY IF Q1227 = 1** | IPVINJF2 |
| Q1241 | Do you think FRIEND 1 gets hit by her sexual partner? | NO  YES | 0  1 | **ASK ONLY IF Q1227 = 2** | VVF2 |
| Q1242 | Do you think FRIEND 2 thinks there are some situations in which it’s ok for her to be hit by her sexual partner? | NO  YES | 0  1 | **ASK ONLY IF Q1227 = 2** | VVINJF2 |
| Q1243 | Has FRIEND 2 discouraged you from hitting your sexual partner? | NO  YES | 0  1 | **ASK ONLY IF Q101 = 1** | IPVADVF2 |
| Q1244 | Has FRIEND 2 encouraged you to request that your sexual partner not hit you? | NO  YES | 0  1 | **ASK ONLY IF Q101 = 2** | = |
| Q1245 | Do you think FRIEND 2 ever had an HIV test? | NO  YES | 0  1 |  | HIVTSTF2 |
| Q1246 | Do you think FRIEND 2 thinks that he/she should have an HIV test? | NO  YES | 0  1 |  | HIVINJF2 |
| Q1247 | Has FRIEND 2 encouraged you to get an HIV test? | NO  YES | 0  1 |  | HIVADVF2 |

Section 13: Attitudes towards HIV Risk Behaviors and Intimate Partner Violence

***Interviewer:***

→ I would like to ask your opinion about certain issues related to behaviors towards sex and your sexual partners. Please tell me how strongly you agree with the following statements:

| **No.** | **Questions and Filters** | **Coding Categories** | **Codes** | **Skip to:** | **VARIABLE** |
| --- | --- | --- | --- | --- | --- |
| Q1301 | I should be using condoms all the time | STRONGLY AGREE  SOMEWHAT AGREE  SOMEWHAT DISAGREE  STRONGLY DISAGREE | 1  2  3  4 |  | ATT_CND |
| Q1302 | It’s ok for me to have more than one sexual partner at the same time | STRONGLY AGREE  SOMEWHAT AGREE  SOMEWHAT DISAGREE  STRONGLY DISAGREE | 1  2  3  4 |  | ATT_MCP |
| Q1303 | There are some situations in which it is ok for me to hit my partner | STRONGLY AGREE  SOMEWHAT AGREE  SOMEWHAT DISAGREE  STRONGLY DISAGREE | 1  2  3  4 | **ASK ONLY IF Q101 = 1** | ATT_IPVM |
| Q1304 | There are some situations in which it is ok for me to be hit by my partner. | STRONGLY AGREE  SOMEWHAT AGREE  SOMEWHAT DISAGREE  STRONGLY DISAGREE | 1  2  3  4 | **ASK ONLY IF Q101 = 2** | ATT_IPVF |

Section 14: Sexual Relationships and Risk Behaviors

***Interviewer:***

→ Now I would like to ask some more personal questions about you and your relationships. Please remember that your answers will be confidential.

| **No.** | **Questions and Filters** | **Coding Categories** | **Codes** | **Skip to:** | **VARIABLE** |
| --- | --- | --- | --- | --- | --- |
| Q1401 | Have you ever had sex?  • Vaginal sex is when a man puts his penis in the vagina of a woman; [some people call this [Swahili term].  • Anal sex is when a man puts his penis in the rectum of a man or a woman; [some people call this [Swahili term]. | NO  YES | 0  1 | **Q1409 and then AND SKIP to SECTION 16** | SEX_EVR |
| Q1402 | How old were you when you had sex for the first time? If you can’t recall the exact age, please give a best estimate. | __ __ YEARS  DON’T KNOW | 88 |  | SEX_AGE |
| Q1403 | How would you describe the first time that you had sex? Would you say that you wanted to have sex, you did not want to have sex but it happened anyway, or were you forced to have sex? | WANTED TO HAVE SEX  DID NOT WANT TO HAVE SEX BUT HAPPENED ANYWAY  WAS FORCED TO HAVE SEX | 1  2  3 |  | SEX_1DES |
| Q1404 | Did you experience any of the following types of situations the first time you had sex?  VERBAL THREATS  PHYSICAL THREATS  PHYSICAL FORCE/HOLDING DOWN  BEATING  HUMILIATING OR DEGRADING SEX ACTS | NO  YES | 0  1 |  | SEX1_VER  SEX1_PHY  SEX1_FRC  SEX1_DEG |
| Q1405 | In total, how many people have you ever had sex with in your lifetime? | __ __ # PERSONS |  | *Note that if this value is less than 3, the participant will only be asked about the corresponding # of partners in the Sexual Network Section | SEXE_NUM |
| Q1406 | In total, how many people have you had sex with in the past 12 months?  This includes people you had sex with only once and people you have had sex with regularly, such as a spouse or someone you live with.  If you can’t recall the exact number, please give a best guess. | NONE  __ __ # PERSONS | 0 |  | SXP12_NUM |
| Q1407 | How many of these partners were women and how many were men? | WOMEN___________  MEN___________ |  | **ASK ONLY IF Q100 = 1**  ***This should total Q1406** | MSM_NUM |
| Q1408 | In general, how would you consider your chances of getting HIV/AIDS? Are they small, moderate, great, or no risk at all? | NO RISK AT ALL  SMALL  MODERATE  GREAT | 1  2  3  4 |  | HIVRISK |
| Q1409 | Have you ever had a test for HIV/AIDS? | NO  YES  DON’T KNOW | 0  1  88 | **Q1501 (UNLESS Q1401 =0)** | TESTHIV |
| Q1410 | How many times have you been tested for HIV/AIDS? | __ __ # TIMES TESTED |  |  | TSTHIV_N |
| Q1411 | Have you had a test for HIV/AIDS in the past 12 months? | NO  YES | 0  1 |  | TEST12M |
| Q1412 | Have you ever received your test results? | NO  YES | 0  1 | **Q1501** | RSLTREC |
| Q1413 | What was the result of your most recent HIV test?  Please remember that everything you say in this interview will be kept in confidence. If you are uncomfortable sharing your result, you may choose to skip this question. | POSITIVE  NEGATIVE  INCONCLUSIVE | 1  2  3 |  | HIVSTAT |
| Q1414 | Who have you shared your HIV/AIDS test results with?  Check all that apply  NO ONE  SPOUSE  BOY/GIRLFRIEND  CASUAL PARTNER  FAMILY (Parents, Children, Siblings, etc.)  RELATIVES (Aunts, Uncles, Cousins, Grandparents, etc.)  FRIEND(S)  HEALTH PROFESSIONAL  OTHER ___________________ | NO  YES | 0  1 |  | HIVDISC  HIVDISC_S |

Section 15. Sexual Network

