**HIV testing**

We will ask men to report at each assessment whether they have ever been tested for HIV, tested within the past 12 months (since last assessment), and whether they received their test results. HIV testing is one of the key HIV prevention strategies that will be promoted by the health leaders. In our previous work, we found that 25% of our population of sexually active youth aged 15-19 had ever been tested for HIV.

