**NOTE: This section should only be asked for participants who have had sex (if Q1401=No, Skip this Section)**

*Interviewer:*

**→** I would now like to ask you about your sexual relationships. When I talk about having sex I mean that you had either vaginal or anal sex with the person.

Many people have different types of sexual partnerships. Some sexual partners are people we have sex with once or twice and some sexual partners are people we have sex with regularly. Some people have many sexual partners and other people have fewer sexual partners. Some people have sex with a partner of the same gender.

In the past 12 months, you mentioned that you have had sex with (Response from Q1406) people. I would like to begin by asking you about the person you have had the longest sexual relationship with during the last 12 months.

| **No.** | **Questions and Filters** | | **Coding Categories** | | **Codes** | **Skip to:** | **VARIABLE** |
| --- | --- | --- | --- | --- | --- | --- | --- |
| PARTNER #1 | | | | | | | |
| Q1501 | | Tell me about the person you have had the longest sexual relationship with. What is the nickname or initials I could use to talk about this person? | PARTNER #1 |  | | ASK ENTIRE SECTION ONLY IF Q1401=1 | NAME_P1 |
| Q1502 | | When was the most recent time you had sex with PARTNER 1? | YEARS AGO__ __  MONTHS AGO__ __  WEEKS AGO__ __  DAYS AGO__ __ |  | |  | RECSEX_P1 |
| Q1503 | | Is PARTNER 1 a man or a woman? | MAN  WOMAN | 1  2 | |  | GEND_P1 |
| Q1504 | | Where did you meet PARTNER 1? | HOME  SCHOOL  WORK  MY CAMP  ANOTHER CAMP  MOSQUE/CHURCH  STREET  CLUB/BAR  GUEST HOUSE  BEACH  PARTY  WEDDING/FUNERAL  OTHER___________________ | 1  2  3  4  5  6  7  8  9  10  11  12  13 | |  | MEET_P1  METP1_S |
| Q1505 | | How long have you been having sex with this partner? | YEARS_________________  MONTHS_______________  WEEKS_________________  DAYS__________________ |  | |  | SEXDY_P1  SEXDM_P1  SEXDW_P1 |
| Q1506 | | What type of relationship do you have with PARTNER 1? | SPOUSE  POLYGAMOUS SPOUSE  COHABITING PARTNER  GIRLFRIEND/BOYFRIEND  FRIEND  CASUAL ACQUAINTANCE  COMMERCIAL SEX WORKER  ONE TIME PARTNER  OTHER___________________ | 1  2  3  4  5  6  7  8  9 | |  | RELP_P1  RELP_P1_S |
| Q1507 | | To the best of your knowledge, how old is _____ PARTNER 1? | __ __ YEARS |  | |  | AGE_P1 |
| Q1508 | | Is PARTNER 1 a member of this camp? | NO  YES  DON’T KNOW | 0  1  88 | |  | CAMPM_P1 |

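### The survey skip for men who have never had sex bypasses the past-12-month testing and results items, so both go unrecorded for those of them not answering NO to ever tested

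*Protocol*

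**What the plan says.** Section 7.4.1 (HIV testing) sets out the outcome for men in general: "We will ask men to report at each assessment whether they have ever been tested for HIV, tested within the past 12 months", glossed there as since the last assessment, together with whether results were received. It does not limit these questions to men who have had sex. Section 3.3 lists uptake of HIV testing and counselling among the secondary endpoints, next to delay of sexual debut. Neither section says whether uptake means ever tested or recently tested.

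The instrument is in Appendix D, Section 14:

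- Q1401 asks about ever having had sex. The skip beside it, which from context belongs to the NO answer, is "Q1409 and then AND SKIP to SECTION 16".
- Q1409 asks "Have you ever had a test for HIV/AIDS" and carries the skip "Q1501 (UNLESS Q1401 =0").
- Q1411 asks "Have you had a test for HIV/AIDS in the past 12 months", and Q1412 asks "Have you ever received your test results". Q1412 has a skip to Q1501 with no exception for men who have never had sex.

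Section 15 of the survey has its own filter: "This section should only be asked for participants who have had sex (if Q1401=No, Skip this Section"). Section 8.2.3 (Behavioral Survey) says the same form serves baseline, 12 months and 30 months.

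**The concern.** On its natural reading the Q1401 skip takes a man who has never had sex from Q1409 straight to Section 16. He does not reach Q1410 to Q1414, even when he has just said he was tested. That contradicts Section 7.4.1 for two of its three testing components.

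The past-12-month item is the one tied to the trial period. Ever tested cannot show a new test in a man who had already been tested before baseline, and the count of tests (Q1410) is skipped as well. The loss is also selective: any recent tester among these men must be among those not answering NO at Q1409, and these are the men whose answer is lost.

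At 12 and 30 months, whether the items are asked depends on sexual debut. Debut by then is a post-randomisation variable, and delaying it is itself a secondary endpoint. An analysis confined to the men who were asked would condition on something the intervention may change.

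**Working it through.** **Who is undetermined.** Take the men who answer NO at Q1401, by their answer at Q1409:

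- NO: never tested, so not tested in the past 12 months, and receipt of results does not arise. Nothing is lost.
- YES: ever tested is known; past-12-month testing and receipt of results are not.
- DON'T KNOW: neither later component is known.

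So the share of all men whose past-12-month status is undetermined is s × t, where s is the share who have never had sex and t is the share of those answering YES or DON'T KNOW at Q1409.

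**Inputs.**

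- Section 9.1.1 gives 36.2 sexually active males out of 52 per camp, and 1955 out of 2808 in 54 camps. These agree: 36.2 × 54 = 1954.8 and 52 × 54 = 2808.
- Ceiling for s: 1 − 36.2/52 = 30.4%. This assumes that every man not counted as sexually active has never had sex. The protocol does not say so, and does not state the never-had-sex share.
- For t, the only testing figure is the 25% ever tested in Section 7.4.1. It comes from sexually active youth aged 15 to 19, so here it is an assumption, shown with a range of 10% to 50%.
- Number of men: 1,249 (Protocol Summary). Section 3.2.3 has 1,252, which makes no material difference.

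**Results at the ceiling s = 30.4%.** Men not asked Q1411 and Q1412: at most 0.3038 × 1,249 = about 379. Past-12-month status undetermined:

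- t = 10%: 0.3038 × 0.10 = 3.0%, about 38 men
- t = 25%: 0.3038 × 0.25 = 7.6%, about 95 men
- t = 50%: 0.3038 × 0.50 = 15.2%, about 190 men

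**If fewer men have never had sex**, at t = 25%: s = 20% gives 5.0%, s = 10% gives 2.5%, and s = 5% gives 1.25%.

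Missing by routing on ever tested: 0% in every case.

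**The case against.** **The skip may mean something else.** Its wording is garbled. It could be read as entering the testing block at Q1409, finishing it, and then bypassing Section 15. Ever-tested men who have never had sex would then get Q1410 to Q1414 and there would be no gap. The missing exception at Q1412 does not rule this out, because Section 15's own filter would catch those men. This reading is possible but less likely: the skip names Q1409 alone, and Q1409 carries an exception that Q1412 lacks, as if these men were not expected to get that far. Even on this reading, the instruction is too unclear to program from.

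**The follow-up form may differ.** Section 6.3 attaches Appendix D to the baseline survey, and items planned for midpoint and endpoint, such as moral agency (Section 7.4.1) and loan experience (Section 7.6.1), are not in it. So the follow-up form must at least contain additions. But Section 8.2.3 says the form is reused, and nothing indicates that this skip would change.

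**Some men can be recovered.** Q1409 is repeated at each wave. A man who says NO at baseline and YES at 12 months was tested in between. This stands, but it does not help for men already tested at baseline. A change between 12 and 30 months places the test within 18 months, not 12. Receipt of results is not recovered at all.

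**A reader might infer that the testing endpoint is missing for about 30% of men.** It is not. Q1409 is put to everyone, uptake is not defined as recent testing, and a NO at Q1409 settles recent testing. The 30% figure would need every man not sexually active to have never had sex, and all of them to answer YES or DON'T KNOW.

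**Conclusion.** The point holds in a limited form. Read literally, the Q1401 skip contradicts Section 7.4.1 and leaves past-12-month testing and receipt of results unrecorded for men who have never had sex and answer YES or DON'T KNOW at Q1409. The size is about 7.6% of men (about 95 of 1,249) at a 25% share, and 3.0% to 15.2% for shares of 10% to 50%. All of these rest on the 30.4% ceiling and shrink in proportion if fewer men have never had sex. The share giving those answers is an assumption throughout.

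A reader might go further and conclude that the randomised comparison is lost, or that the effect on testing is diluted by a calculable amount. The protocol supports neither. Ever tested stays comparable in all men, and recent testing is known for every never-tested man. Dropping all men who have never had sex, or coding as untested a man who has just said he was tested, would be an analyst's choice that the protocol does not make. Any dilution figure would also need testing rates that it does not give. What remains is a risk of bias in one component of one secondary endpoint if the analysis is restricted to men who were asked.

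**What to change.** - Replace the Q1401 = NO instruction with: ask Q1409; if YES, ask Q1410 to Q1414; then go to Section 16.
- Add the exception for Q1401 = 0 at Q1412, as Q1409 already has it, so that these men go to Section 16 and not to Q1501.
- Apply the same routing to the 12-month and 30-month forms.
- Analyse past-12-month testing in all men, counting Q1409 = NO as not tested, rather than only in men who were asked Q1411.

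After this change no past-12-month answer is missing by routing among men who answer YES or NO at Q1409. Men answering DON'T KNOW remain undetermined.

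The cost is an edit to the tablet program and at most five short questions, put only to ever-tested men who have never had sex.

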**NOTE: This section should only be asked for participants who have had sex (if Q1401=No, Skip this Section)**

*Interviewer:*

**→** I would now like to ask you about your sexual relationships. When I talk about having sex I mean that you had either vaginal or anal sex with the person.

Many people have different types of sexual partnerships. Some sexual partners are people we have sex with once or twice and some sexual partners are people we have sex with regularly. Some people have many sexual partners and other people have fewer sexual partners. Some people have sex with a partner of the same gender.

In the past 12 months, you mentioned that you have had sex with (Response from Q1406) people. I would like to begin by asking you about the person you have had the longest sexual relationship with during the last 12 months.

| **No.** | **Questions and Filters** | | **Coding Categories** | | **Codes** | **Skip to:** | **VARIABLE** |
| --- | --- | --- | --- | --- | --- | --- | --- |
| PARTNER #1 | | | | | | | |
| Q1501 | | Tell me about the person you have had the longest sexual relationship with. What is the nickname or initials I could use to talk about this person? | PARTNER #1 |  | | ASK ENTIRE SECTION ONLY IF Q1401=1 | NAME_P1 |
| Q1502 | | When was the most recent time you had sex with PARTNER 1? | YEARS AGO__ __  MONTHS AGO__ __  WEEKS AGO__ __  DAYS AGO__ __ |  | |  | RECSEX_P1 |
| Q1503 | | Is PARTNER 1 a man or a woman? | MAN  WOMAN | 1  2 | |  | GEND_P1 |
| Q1504 | | Where did you meet PARTNER 1? | HOME  SCHOOL  WORK  MY CAMP  ANOTHER CAMP  MOSQUE/CHURCH  STREET  CLUB/BAR  GUEST HOUSE  BEACH  PARTY  WEDDING/FUNERAL  OTHER___________________ | 1  2  3  4  5  6  7  8  9  10  11  12  13 | |  | MEET_P1  METP1_S |
| Q1505 | | How long have you been having sex with this partner? | YEARS_________________  MONTHS_______________  WEEKS_________________  DAYS__________________ |  | |  | SEXDY_P1  SEXDM_P1  SEXDW_P1 |
| Q1506 | | What type of relationship do you have with PARTNER 1? | SPOUSE  POLYGAMOUS SPOUSE  COHABITING PARTNER  GIRLFRIEND/BOYFRIEND  FRIEND  CASUAL ACQUAINTANCE  COMMERCIAL SEX WORKER  ONE TIME PARTNER  OTHER___________________ | 1  2  3  4  5  6  7  8  9 | |  | RELP_P1  RELP_P1_S |
| Q1507 | | To the best of your knowledge, how old is _____ PARTNER 1? | __ __ YEARS |  | |  | AGE_P1 |
| Q1508 | | Is PARTNER 1 a member of this camp? | NO  YES  DON’T KNOW | 0  1  88 | |  | CAMPM_P1 |
| Q1509 | | Are you still having sex with PARTNER 1? | NO  YES | 0  1 | |  | SEXCUR_P1 |
| Q1510 | | How often do/did you have sex with PARTNER 1? | EVERY DAY  A FEW TIMES A WEEK  FEW TIMES A MONTH  ABOUT ONCE A MONTH  ONLY 1-2 TIMES EVER | 1  2  3  4  5 | |  | SEXFRQ_P1 |
| Q1511 | | During the last (most recent) time you had sex with this partner, did you use a condom? | NO  YES  DON’T KNOW | 0  1  88 | |  | CNDUSE_P1 |
| Q1512 | | How many times would you say you had sex with PARTNER 1 during the last one month you had sex with him/her? | _____________ |  | |  | NUMSEX_P1 |
| Q1513 | | Of these (Response from Q1512) times, how many times would you say you used a condom? | _____________ |  | |  | NUMCND_P1 |
| Q1514 | | Did you ever give PARTNER 1 money in exchange for having sex with you? | NO  YES | 0  1 | |  | GIVFSP_P1 |
| Q1515 | | Did PARTNER 1 ever give YOU money in exchange for having sex? | NO  YES | 0  1 | |  | RECFSP_P1 |
| Q1516 | | Did you use a condom the last time money was given or exchanged for sex with PARTNER 1? | NO  YES | 0  1 | | **ASK ONLY IF either Q1514 or Q1515 =1** | CNDM_P1 |
| Q1517 | | The last time you had sex with PARTNER 1, did you drink alcohol before or during sex? | NO  YES | 0  1 | |  | DRNK1_P1 |
| Q1518 | | The last time you had sex with PARTNER 1, did PARTNER 1 drink alcohol before or during sex with you? | NO  YES  DON’T KNOW | 0  1  88 | |  | DRINK2_P1 |
| Q1519 | | While you were in a sexual relationship with PARTNER 1, did you have sex with anybody else? | NO  YES | 0  1 | |  | SXCUR_P1 |
| Q1520 | | As far as you know, during the time you were having a sexual relationship with PARTNER 1, do you think PARTNER 1 had sex with other people? | NO  YES | 0  1 | |  | MCP_P1 |
| Q1521 | | How confident are you that you can use a condom with PARTNER 1? | VERY CONFIDENT  SOMEWHAT CONFIDENT  NOT AT ALL CONFIDENT | 1  2  3 | |  | UCND_P1 |
| Q1522 | | How confident are you that you can discuss HIV with PARTNER 1? | VERY CONFIDENT  SOMEWHAT CONFIDENT  NOT AT ALL CONFIDENT | 1  2  3 | |  | TLKHIV_P1 |
| Q1523 | | Have you ever discussed getting an HIV test with PARTNER 1? | NO  YES | 0  1 | |  | TLKTST_P1 |
| Q1524 | | Have you ever gone together with PARTNER 1 for an HIV test? | NO  YES | 0  1 | |  | TOGTST_P1 |
| Q1525 | | Has PARTNER 1 shared the results of their HIV test in the past 12 months? | NO  YES | 0  1 | |  | TSTDISC_P1 |
| Q1526 | | In the past 12 months, has PARTNER 1 ever hit, slapped, kicked, pushed, shoved or otherwise physically hurt you? | NO  YES | 0  1 | |  | VICVIO_P1 |
| Q1527 | | In the past 12 months, have you ever hit, slapped, kicked, pushed, shoved or otherwise physically hurt PARTNER 1? | NO  YES | 0  1 | |  | PERVIO_P1 |
| PARTNER #2  *Interviewer:*  **→** Now lets talk about your other most recent partners (excluding the partner we just talked about). | | | | | | | |
| Q1528 | | Tell me about the person you had sex with most recently within the last 12 months who is not PARTNER 1. What is the nickname or initials I could use to talk about this person? | PARTNER #2 | |  |  | NAME_P2 |
| Q1529 | | When was the most recent time you had sex with PARTNER 2? | MONTHS __ __  WEEKS __ __  DAYS __ __ | |  |  | RECSEX_P2 |
| Q1530 | | Is PARTNER 2 a man or a woman? | MAN  WOMAN | | 1  2 |  | GEND_P2 |
| Q1531 | | Where did you meet PARTNER 2? | HOME  SCHOOL  WORK  MY CAMP  ANOTHER CAMP  MOSQUE/CHURCH  STREET  CLUB/BAR  GUEST HOUSE  BEACH  PARTY  WEDDING/FUNERAL  OTHER___________________ | | 1  2  3  4  5  6  7  8  9  10  11  12  13 |  | MEET_P2  METP1_S |
| Q1532 | | How long have you been having sex with this partner? | YEARS_________________  MONTHS_______________  WEEKS_________________ | |  |  | SEXDY_P2  SEXDM_P2  SEXDW_P2 |
| Q1533 | | What type of relationship do you have with PARTNER 2? | SPOUSE  POLYGAMOUS SPOUSE  COHABITING PARTNER  GIRLFRIEND/BOYFRIEND  FRIEND  CASUAL ACQUAINTANCE  COMMERCIAL SEX WORKER  ONE TIME PARTNER  OTHER___________________ | | 1  2  3  4  5  6  7  8  9 |  | RELP_P2  RELP_P2_S |
| Q1534 | | (If needed: To the best of your knowledge) How old is _____ PARTNER 2)? | __ __ YEARS | |  |  | AGE_P2 |
| Q1535 | | Is PARTNER 2 a member of this camp? | NO  YES  DON’T KNOW | | 0  1  88 |  | CAMPM_P2 |
| Q1536 | | Are you still having sex with PARTNER 2? | NO  YES | | 0  1 |  | SEXCUR_P2 |
| Q1537 | | How often do/did you have sex with PARTNER 2? | EVERY DAY  A FEW TIMES A WEEK  FEW TIMES A MONTH  ABOUT ONCE A MONTH  ONLY 1-2 TIMES EVER | | 1  2  3  4  5 |  | SEXFRQ_P2 |
| Q1538 | | During the last (most recent) time you had sex with this partner, did you use a condom? | NO  YES  DON’T KNOW | | 0  1  88 |  | CNDUSE_P2 |
| Q1539 | | How many times would you say you had sex with PARTNER 2 during the last one month you had sex with him/her? | _____________ | |  |  | NUMSEX_P2 |
| Q1540 | | Of these (Response from Q1539) times, how many times would you say you used a condom? | _____________ | |  |  | NUMCND_P2 |
| Q1541 | | Did you ever give PARTNER 2 money in exchange for having sex with you? | NO  YES | | 0  1 |  | GIVFSP_P2 |
| Q1542 | | Did PARTNER 2 ever give YOU money in exchange for having sex? | NO  YES | | 0  1 |  | RECFSP_P2 |
| Q1543 | | Did you use a condom the last time money was given or exchanged for sex with PARTNER 2? | NO  YES | | 0  1 | **ASK ONLY IF either Q1542 or Q1543 =1** | CNDM_P2 |
| Q1544 | | The last time you had sex with PARTNER 2, did you drink alcohol before or during sex | NO  YES | | 0  1 |  | DRNK1_P2 |
| Q1545 | | The last time you had sex with PARTNER 2, did PARTNER 2 drink alcohol before or during sex with you? | NO  YES  DON’T KNOW | | 0  1  88 |  | DRINK2_P2 |
| Q1546 | | While you were in a sexual relationship with PARTNER 2, did you have sex with anybody else? | NO  YES | | 0  1 |  | SXCUR_P2 |
| Q1547 | | As far as you know, during the time you were having a sexual relationship with PARTNER 2, do you think PARTNER 2 had sex with other people? | NO  YES | | 0  1 |  | MCP_P2 |
| Q1548 | | How confident are you that you can use a condom with PARTNER 2? | VERY CONFIDENT  SOMEWHAT CONFIDENT  NOT AT ALL CONFIDENT | | 1  2  3 |  | UCND_P2 |
| Q1549 | | How confident are you that you can discuss HIV with PARTNER 2? | VERY CONFIDENT  SOMEWHAT CONFIDENT  NOT AT ALL CONFIDENT | | 1  2  3 |  | TLKHIV_P2 |
| Q1550 | | Have you ever discussed getting an HIV test with PARTNER 2? | NO  YES | | 0  1 |  | TLKTST_P2 |
| Q1551 | | Have you ever gone together with PARTNER 2 for an HIV test? | NO  YES | | 0  1 |  | TOGTST_P2 |
| Q1552 | | Has PARTNER 2 shared the results of their HIV test in the past 12 months? | NO  YES | | 0  1 |  | TSTDISC_P2 |
| Q1553 | | In the past 12 months, has PARTNER 2 ever hit, slapped, kicked, pushed, shoved or otherwise physically hurt you? | NO  YES | | 0  1 |  | VICVIO_P2 |
| Q1554 | | In the past 12 months, have you ever hit, slapped, kicked, pushed, shoved or otherwise physically hurt PARTNER 2? | NO  YES | | 0  1 |  | PERVIO_P2 |
| PARTNER #3 | | | | | | | |
| Q1555 | | Tell me about another person you had sex with most recently before PARTNER 2. What is the nickname or initials I could use to talk about this person? | PARTNER #3 | |  |  | NAME_P3 |
| Q1556 | | When was the most recent time you had sex with PARTNER 3? | MONTHS __ __  WEEKS __ __  DAYS __ __ | |  |  | RECSEX_P3 |
| Q1557 | | Is PARTNER 3 a man or a woman? | MAN  WOMAN | | 1  2 |  | GEND_P3 |
| Q1558 | | Where did you meet PARTNER 3? | SCHOOL  WORK  MY CAMP  ANOTHER CAMP  MOSQUE/CHURCH  STREET  CLUB/BAR  GUEST HOUSE  BEACH  PARTY  WEDDING/FUNERAL  OTHER___________________ | | 1  2  3  4  5  6  7  8  9  10  11  12 |  | MEET_P3  METP1_S |
| Q1559 | | How long have you been having sex with this partner? | YEARS_________________  MONTHS_______________  WEEKS_________________ | |  |  | SEXDY_P3  SEXDM_P3  SEXDW_P3 |
| Q1560 | | What type of relationship do you have with PARTNER 3? | SPOUSE  POLYGAMOUS SPOUSE  COHABITING PARTNER  GIRLFRIEND/BOYFRIEND  FRIEND  CASUAL ACQUAINTANCE  COMMERCIAL SEX WORKER  ONE TIME PARTNER  OTHER___________________ | | 1  2  3  4  5  6  7  8  9 |  | RELP_P3  RELP_P3_S |
| Q1561 | | (If needed: To the best of your knowledge) How old is _____ PARTNER 3)? | __ __ YEARS | |  |  | AGE_P3 |
| Q1562 | | Is PARTNER 3 a member of this camp? | NO  YES  DON’T KNOW | | 0  1  88 |  | CAMPM_P3 |
| Q1563 | | Are you still having sex with PARTNER 3? | NO  YES | | 0  1 |  | SEXCUR_P3 |
| Q1564 | | How often do/did you have sex with PARTNER 3? | EVERY DAY  A FEW TIMES A WEEK  FEW TIMES A MONTH  ABOUT ONCE A MONTH  ONLY 1-2 TIMES EVER | | 1  2  3  4  5 |  | SEXFRQ_P3 |
| Q1565 | | During the last (most recent) time you had sex with this partner, did you use a condom? | NO  YES  DON’T KNOW | | 0  1  88 |  | CNDUSE_P3 |
| Q1566 | | How many times would you say you had sex with PARTNER 3 during the last one month you had sex with him/her? | _____________ | |  |  | NUMSEX_P3 |
| Q1567 | | Of these (Response from Q1566) times, how many times would you say you used a condom? | _____________ | |  |  | NUMCND_P3 |
| Q1568 | | Did you ever give PARTNER 3 money in exchange for having sex with you? | NO  YES | | 0  1 |  | GIVFSP_P3 |
| Q1569 | | Did PARTNER 3 ever give YOU money in exchange for having sex? | NO  YES | | 0  1 |  | RECFSP_P3 |
| Q1570 | | Did you use a condom the last time money was given or exchanged for sex with PARTNER 3? | NO  YES | | 0  1 | **ASK ONLY IF either Q1570 or Q1571 =1** | CNDM_P3 |
| Q1571 | | The last time you had sex with PARTNER 3, did you drink alcohol before or during sex | NO  YES | | 0  1 |  | DRNK1_P3 |
| Q1572 | | The last time you had sex with PARTNER 3, did PARTNER 3 drink alcohol before or during sex with you? | NO  YES  DON’T KNOW | | 0  1  88 |  | DRINK2_P3 |
| Q1573 | | While you were in a sexual relationship with PARTNER 3, did you have sex with anybody else? | NO  YES | | 0  1 |  | SXCUR_P3 |
| Q1574 | | As far as you know, during the time you were having a sexual relationship with PARTNER 3, do you think PARTNER 3 had sex with other people? | NO  YES | | 0  1 |  | MCP_P3 |
| Q1575 | | How confident are you that you can use a condom with PARTNER 3? | VERY CONFIDENT  SOMEWHAT CONFIDENT  NOT AT ALL CONFIDENT | | 1  2  3 |  | UCND_P3 |
| Q1576 | | How confident are you that you can discuss HIV with PARTNER 3? | VERY CONFIDENT  SOMEWHAT CONFIDENT  NOT AT ALL CONFIDENT | | 1  2  3 |  | TLKHIV_P3 |
| Q1577 | | Have you ever discussed getting an HIV test with PARTNER 3? | NO  YES | | 0  1 |  | TLKTST_P3 |
| Q1578 | | Have you ever gone together with PARTNER 3 for an HIV test? | NO  YES | | 0  1 |  | TOGTST_P3 |
| Q1579 | | Has PARTNER 3 shared the results of their HIV test in the past 12 months? | NO  YES | | 0  1 |  | TSTDISC_P3 |
| Q1580 | | In the past 12 months, has PARTNER 3 ever hit, slapped, kicked, pushed, shoved or otherwise physically hurt you? | NO  YES | | 0  1 |  | VICVIO_P3 |
| Q1581 | | In the past 12 months, have you ever hit, slapped, kicked, pushed, shoved or otherwise physically hurt PARTNER 3? | NO  YES | | 0  1 |  | PERVIO_P3 |

Section 16: Work and Expenditures

